#### Psychological wellbeing

*The Strengths and Difficulties Questionnaires (SDQ) [36].* The self-report and parent-report versions will be used to assess the child’s psychological wellbeing. It is a brief behavioural screening questionnaire for children and young people ages 2 -17. The 25 items are divided between 5 scales (emotional, conduct problems, hyperactivity/inattention, peer relationship problems, prosocial behaviour), with the first four summed to provide a total difficulties score. The SDQ has an ‘impact scale’, which assesses the impact that symptoms have on everyday life in a range of domains (home, school, leisure). The SDQ has good internal consistency (mean Cronbach α .73), cross-informant correlation (mean 0.34), and retest stability after 4 to 6 months [36].

*The Revised Child Anxiety and Depression Scale (RCADS)*. The parent and self-report versions will be used to assess the child’s anxiety and depression. It is a 47-item questionnaire for 8–18-year-olds. Its subscales include separation anxiety disorder, social phobia, generalized anxiety disorder, panic disorder, obsessive compulsive disorder, and low mood (major depressive disorder). In addition to the subscales, a total anxiety scale and total anxiety and depression scale can be calculated. It has good reliability on subscales and total scale, with internal consistency of adequate-excellent across the different subscales [56]. It also had good test-retest reliability and good convergent and concurrent validity [56, 57].

#### Sample characterisation

*Demographic questionnaire*. Parents/carers will be asked to complete a demographic questionnaire. This will ask about the child’s age, gender, ethnic background, existing child psychiatric diagnoses, parent/carer’s age, family composition, parent/carer’s education level, parent/carer employment status and household income band.

The Generalised Anxiety Disorder Assessment (GAD-7) [58]

The measure will be used to assess the parents/carers self-reported anxiety. The GAD-7 is a 7-item measure with scores ranging from 0–21. Scores of 5, 10, and 15 represent cut-points for mild, moderate, and severe anxiety, respectively. The measure has been shown to have excellent internal consistency and good test-retest reliability and convergent validity [58].

The Patient Health Questionnaire (PHQ-9) [59]

The measure will be used to assess the parent/carers self-reported depression. It is a 9-item measure of depressive symptoms with scores ranging from 0–27. Each item asks the individual to rate the severity of their symptoms over the past two weeks. Scores of 5, 10, and 15 and 20 represent cut-points for mild, moderate, moderately severe and severe depression respectively. The PHQ-9 has demonstrated good convergent and discriminant validity and high internal consistency [59–61].

*UCLA-LS-3 [35].* This measure will also be used to characterise the level of self-reported parent/carer loneliness.

#### Process measures

*Goal based outcomes [47].* During their first intervention session young people will be asked to identify 3 intervention goals relating to their loneliness. They will be asked to rate on a 1–10 scale where they are in terms of achieving this goal; with 1 being “the furthest I could ever be from achieving this goal” and 10 “I have achieved this goal”. They will then rate each goal as part of the routine outcome measures for each session. Goal-based outcomes have been shown to improve treatment retention, clinical outcomes and client progress [62, 63].

*Visual analogue scales (VAS) [48].* For each session young people will be asked to rate their current mood, anxiety and loneliness on a 1–10 scale, where 10 is the worst. Visual analogue scales have been shown to have good validity and reliability [64].

#### Feasibility and experience measures

During the post-intervention assessment, the participants will be asked to complete the child and parent-report versions of the Experience of Services Questionnaire (ESQ) [39] regarding their experience of the intervention. Feasibility will be assessed based upon recruitment (meeting targets), retention, completion of measures and proportion of sessions attended by the participants. All participating families will also be asked how COVID-19 or other events have impacted the child’s loneliness during the intervention period. Finally, any adverse events that occur during the trial period will be recorded, reported and discussed within supervision.

### Data analysis

#### Primary outcome measure

The primary outcome measure of the SCED (self-reported scores on the Three Item Loneliness Scale [34]) will be analysed using visual inspection and statistical analysis.

For visual analysis, in accordance with SCED procedure, each participants data will be graphically represented on a line graph for the outcome variable [65, 66]. The baseline phase will be examined to determine a stable control. Data within and between each phase will then be compared for a) change in trend or symptom severity across phases, b) the degree of the slope on the graph which indicates the strength of the trend and c) change in the variability of the data to indicate stability in symptom change. Data will be mapped and inspected using both within-phase (evaluation of data patterns across participants in a single phase) and between-phase (comparison across adjacent phases for each participant) analyses [65, 66].

For statistical analysis Tau-U [45] will be used, which is a test specifically designed for single case research and has been used in previous SCEDs of psychological interventions [67, 68]. It is not dependent on distribution assumptions and calculations are based upon consideration of all data points. A further strength of the approach is that it can control for unwanted trends or variability in baseline scores to identify whether any change is the result of the introduction of the intervention [45]; making it a robust approach for SCED analysis. Tau-U will be used to analyse the overlap between the baseline and intervention phase and the baseline and post-intervention phase. The statistical analysis can be understood as the percentage of data that ‘improves’ across the phases of the study whilst considering any pre-existing baseline trends [68]. Tau-U will also be used to calculate an effect size and weighted average across all cases for the primary outcome variable.

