### Aims and objectives

The primary objective will be to evaluate the efficacy of CBT for loneliness in children and young people ages 11–18. The primary outcome will be differences in scores on the Three-Item Loneliness Scale [34] between baseline and intervention and baseline and post-intervention. It is hypothesised that there will be a significant decrease in self-reported loneliness across both time-points. The secondary outcomes will be self-reported loneliness scores on the UCLA Loneliness Scale (UCLA-LS-3) [35] and self and parent-reported scores on the Strengths and Difficulties Questionnaires (SDQ) [36] and Revised Child Anxiety and Depression Scale (RCADS) [37]. It is hypothesised that there will be a reliable and clinically meaningful change [38] in total loneliness scores on the UCLA-LS-3, in the impact scores on the SDQ and in total anxiety and depression scores on the RCADS.

The secondary objective is to evaluate the feasibly and acceptability of the intervention process. This will be defined in terms of a) meeting the recruitment target, b) participant retention and c) participant feedback of the intervention using the Experience of Service Questionnaire [39].

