## Methods

### Study design

The efficacy of CBT for loneliness in children and young people will be evaluated through a randomised multiple-baseline single-case experimental design (SCED) [28–30]. The design consists of AB+ post-intervention, where A is the baseline phase, B is the intervention phase and then a post-intervention phase. In the SCED approach participants are repeatedly assessed on at least one independent variable, in this case self-reported loneliness on the Three-item Loneliness Scale [34], across each phase of the intervention. This repeated measurement and within subject replication is then used to test the effects of the intervention for individual participants [28, 30]. Multiple-baseline SCEDs are a controlled experimental approach, with multiple-baselines protecting against threats to internal validity [40].

The construction of this SCED trial and the reporting of the results will be in accordance with the Single-Case Reporting Guidelines in Behavioural Intervention (SCRIBE) [30].

The study has received ethical approval from Royal Holloway, University of London on 22.03.2021 (ethical approval number: 2489). The study was registered with ClinicalTrials.gov on 07.12.2021 (registration number: NCT05149963).

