**Fig 1 pone.0278746.g001:**
[figure not shown]
Showing the trials schedule of enrolment, interventions and assessments.

Participants will be recruited via advertisements emailed to schools, shared via social media and word of mouth. Participants and their parents/carers will be sent an electronic information sheet and given the opportunity to ask any questions before completing an online consent form. Participants will provide informed ascent as they are under 18, with parents/carers providing informed consent. Participants and their parents/carers will then complete a baseline eligibility assessment. They will complete a range of online questionnaires via Qualtrics [41], a secure online platform. They will then attend a remote research assessment appointment to determine whether the family meet the eligibility criteria. The researcher completing the baseline and post-intervention assessments will not be involved in the clinical intervention and will be blinded to baseline allocation. After all baseline assessments for the participant group are completed, they will be discussed within supervision to confirm that the participants meet eligibility criteria. Eligible participants will then be randomised using a random number generator to one of four different baseline lengths (12 days, 19 days, 26 days or 33 days [42]. The decision to have a minimum of 12 observations per phase meets the requirements for guidelines and standards [43] and will allow for sufficient power for Tau-U analysis [44, 45].

Each of the families will then be contacted to inform them of their allocation. Randomisation and contacting of the families will be completed by a third researcher, who is not involved in either the clinical intervention or research assessments. Families will receive a £25 voucher for completing the baseline eligibility assessment. A letter will also be sent to their General Practitioner (GP) informing them of the family’s participation in the research study. The setting for the entire study will be remote via Zoom [46], with participants recruited from across the United Kingdom (UK).

All participants in the group will begin their baseline phase concurrently. During the baseline phase participants will be asked to complete the Three-Item Loneliness Scale [34] each day via Qualtrics [41]. SMS message reminders will also be sent to the young people and their parent/carers each day.

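### Tau-U significance tests assume independent ratings, so their error rate depends on an autocorrelation the plan ignores, and the randomised baseline lengths are not used for inference

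*Protocol article*

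**What the plan says.** Under Aims and objectives the protocol article sets a hypothesis in terms of significance for two contrasts, baseline to intervention and baseline to post-intervention: "It is hypothesised that there will be a significant decrease in self-reported loneliness across both time-points".

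Under Data analysis, Primary outcome measure, visual inspection is paired with one statistical method: "For statistical analysis Tau-U [45] will be used, which is a test specifically designed for single case research". Its merits are given as "It is not dependent on distribution assumptions and calculations are based upon consideration of all data points" and, on baseline trend, "it can control for unwanted trends or variability in baseline scores to identify whether any change is the result of the introduction of the intervention". It is applied to both contrasts ("Tau-U will be used to analyse the overlap between the baseline and intervention phase and the baseline and post-intervention phase") and pooled ("Tau-U will also be used to calculate an effect size and weighted average across all cases for the primary outcome variable"). Serial dependence is not mentioned.

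Under Procedure, "Eligible participants will then be randomised using a random number generator to one of four different baseline lengths": 12, 19, 26 or 33 days. Participants in the group start baseline at the same time. The Three-Item Loneliness Scale is completed daily in baseline, once per session during the intervention, and daily for 12 days afterwards. Under Study design the claim is that "Multiple-baseline SCEDs are a controlled experimental approach, with multiple-baselines protecting against threats to internal validity".

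**The concern.** A Tau-U p-value compares a count of pairwise improvements with a standard error derived for independent observations. Ratings of the same three items by one adolescent on successive days are likely to be positively correlated. If they are, the true variance of the count exceeds the assumed one, and p-values and intervals are too small and too narrow. Every case shares the same understatement, so a weighted average over cases inherits it.

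The trial also creates a source of valid inference, the random choice of baseline length, and then does not use it in the analysis described. The protection claimed for the staggered baselines reaches only one of the two primary contrasts.

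The primary efficacy conclusion is at stake. Under Limitations, the move to an open trial and then a randomised trial depends on preliminary evidence of effectiveness.

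**Working it through.** **The plan's own figure.** Procedure states that at least 12 observations per phase give sufficient power for Tau-U. No power, effect size, alpha or autocorrelation is given, so the statement cannot be reproduced. Under independence, SE(Tau) = √[(nA + nB + 1)/(3·nA·nB)]. For 12 versus 12 this is √(25/432) = 0.241. The Tau detectable with 80% power at two-sided 5% is (1.960 + 0.842) × 0.241 ≈ 0.67. This also rests on independence.

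**Inputs from the protocol article.**
- Baseline: 12, 19, 26 or 33 daily ratings.
- Intervention: about 12 ratings, one per session (4 bi-weekly, 4 weekly, 4 fortnightly).
- Post-intervention: 12 daily ratings.
- Score: integer 0–12. Cases: 6–8.

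**Assumptions.** Two-sided 5%; no treatment effect; a stationary first-order autoregressive daily series with lag-1 correlation r. The documents give no r, so a range is shown.

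**Simulated rejection rates per case**, with z = S/√[nA·nB·(nA + nB + 1)/3] and |z| > 1.96, over the four baseline lengths:

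| r | Baseline vs post-intervention | Baseline vs intervention |
|---|---|---|
| 0 | about 4–5% | about 4–5% |
| 0.2 | about 9–10% | about 6–7% |
| 0.3 | about 13–14% | about 7–9% |
| 0.5 | about 23–24% | about 10–14% |

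The second contrast is inflated less because its intervention ratings are days or weeks apart. Reading bi-weekly as twice a week or as every two weeks changes little.

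**Hand check of the daily-versus-daily column.** For a difference between two means of n = 12 daily values, the variance is multiplied by V = 1 + 2·Σ(1 − k/n)·r^k, k = 1 to 11, and the rejection rate is about 2·[1 − Φ(1.96/√V)].
- r = 0.2: V = 1.45, rate 10.3%.
- r = 0.3: V = 1.76, rate 13.9%.
- r = 0.5: V = 2.67, rate 23.0%.

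These are means, not pair counts, but they agree with the simulation.

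**Trend correction.** Using S_AB − S_AA, with nA(nA − 1)(2nA + 5)/18 added to the variance, rejection at r = 0.2–0.5 is 1.9 to 4.7 times nominal for baseline versus post-intervention and 1.3 to 2.9 times for baseline versus intervention. The inflation remains.

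**Pooling over 6–8 cases (inverse variance).** Baseline versus post-intervention rejects 9–11% at r = 0.2 and 21–22% at r = 0.5. Baseline versus intervention rejects about 6% and 11–12%.

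**What the stagger controls.** The longest baseline ends on day 33. After the shortest baseline, 12 sessions with bi-weekly read as twice a week end near day 12 + 3 × 3.5 + 4 × 7 + 4 × 14 = 106.5. With bi-weekly read as every two weeks, this is 12 + 3 × 14 + 28 + 56 = 138. On either reading nobody in the group is still in baseline when anyone's post-intervention phase begins, so that contrast has no concurrent control.

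**What the randomisation can support.** If lengths are drawn independently there are 4⁶ = 4,096 to 4⁸ = 65,536 allocations. If two per length were fixed at N = 8 there would be 8!/(2!)⁴ = 2,520. A pooled randomisation test for baseline versus intervention (summed before-after mean difference, one-sided 5%, ratings as already scheduled) rejected 3.7–5.7% under the null with 6 cases and 4.2–4.7% with 8, for r from 0 to 0.7. Its power for an immediate 1-SD drop at r = 0.3 (both assumed) was about 82% with 6 cases and 90% with 8. A single case has four possible start points, so its smallest p-value is 1/4 = 0.25.

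**The case against.** The documents report no autocorrelation, and at zero the test holds its level. A reader might infer that false positives rise two- to five-fold across the primary analysis. The documents do not support that: such a multiple fits only baseline versus post-intervention, and only at an assumed r of about 0.2–0.5. Over the same range baseline versus intervention is about 1.1- to 2.8-fold. This objection stands, and the size is therefore stated conditionally and by contrast.

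A reader might also infer that the unused randomisation would repair everything. It would not. It randomises the start of the intervention, so it supports only a pooled baseline-versus-intervention test. It says nothing valid about the post-intervention contrast, where the inflation is larger, and cannot yield a significant single-case result.

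Model-based alternatives are not exact either. In short series with r = 0.5, a level-change model with AR(1) errors fitted by REML still rejected about 8–11%, and a maximum-likelihood fit 16%, against about 23–25% for Tau-U.

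It can further be said that the quoted sentence is true as far as it goes, that visual inspection accompanies the test, that the authors urge caution, and that variance details belong in an analysis plan. The first three are fair and temper the consequence. The last does not dispose of the point: the article itself chooses the test, gives the rationale, calls the approach robust and sets a significance hypothesis. Following it as written would understate error if ratings are correlated.

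**Conclusion.** The concern holds in conditional form. Standard Tau-U p-values and intervals require serial independence, and none of the stated strengths (no distribution assumptions, trend control, weighted averaging) supplies it. If daily lag-1 autocorrelation is 0.2–0.5, nominal 5% becomes about 9–24% for baseline versus post-intervention and about 6–14% for baseline versus intervention. At zero there is no inflation. These sizes rest on a first-order autoregressive model and a two-sided 5% level, neither of which the documents state.

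Two design conclusions need no such assumption. The randomised baseline lengths are not used in the analysis described. And the multiple baselines control only the baseline-to-intervention contrast, so the statement on internal validity does not extend to baseline versus post-intervention.

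**What to change.** Amend Data analysis, Primary outcome measure, as follows.

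- Keep Tau-U and its weighted average as descriptive effect sizes, without the standard p-values and intervals.
- Make the inferential test for baseline versus intervention a single pooled randomisation test over the baseline-length allocations, redrawn by the procedure actually used, on the ratings already planned. State that procedure: the reference set is 4⁶ to 4⁸ under independent draws and 2,520 only under fixed balance at N = 8. Because rating changes from daily to per session at the allocated start, exactness is not automatic, although the simulated size stayed near 5%.
- Describe baseline versus post-intervention as an uncontrolled before-after comparison.
- Report a p-value for that contrast, or for any single case, only from a method that allows for autocorrelation, for example REML with AR(1) errors and a small-sample correction, and call it approximate.

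The cost is revised wording and a short analysis script. Daily ratings during the intervention are not required, so participant burden is unchanged. The downside is that significance claims become less favourable and no single case can reach significance by the randomisation test.

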The baseline phase will be immediately followed by the intervention. Each family will receive (on average) 12 sessions of CBT for loneliness in children and young people. Where possible the first 4 sessions will take place bi-weekly, the second 4 sessions weekly and the final 4 sessions fortnightly.

For all participants the first two sessions will be focussed on assessment and then formulation. The final session for all participants will focus on relapse prevention. During the assessment session the participant will be asked to define 3 goal-based outcomes (GBOs) [47] for how they hope the intervention will reduce their loneliness, which will then guide the treatment process. During the intervention phase the participants will complete routine outcome measures (ROMs) for each session. This will include the Three-Item Loneliness Scale [34], visual analogue scales (VAS) of mood, anxiety and loneliness and ratings of their goal-based outcomes [48]. The ROMs will be completed via Qualtrics [41] before each session. If participants have not completed the ROMs before their appointment, then they will be completed with the clinician at the start of the session.

Participants will begin the post-intervention phase immediately after the final session of their intervention. During the post-intervention phase participants will be asked to complete the primary outcome measure, Three-Item Loneliness Scale [34], each day for 12 days. They will then complete their post-intervention assessment with the second researcher. Before the assessment they will be asked to re-complete the baseline questionnaires in addition to the parent and child-report versions of the Experience of Service Questionnaire [39] and a questionnaire asking whether COVID-19 or any other events have affected them during the intervention period. The family will be given a £25 voucher for completing the post-intervention assessment. A letter will be sent to their General Practitioner (GP) informing them of their participation in the research study has finished.

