### Participants

We will aim to recruit 6–8 participants to the study. All participants will be recruited from within the United Kingdom. Participants must meet the following inclusion/exclusion criteria:

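### Baseline-corrected Tau-U does not remove a trend that continues past the baseline, so on its own it cannot show that change results from the intervention

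*Protocol article*

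**What the plan says.** Under Data analysis, Primary outcome measure, the protocol gives this as a strength of Tau-U: "it can control for unwanted trends or variability in baseline scores to identify whether any change is the result of the introduction of the intervention", and on that ground calls the approach robust. Two contrasts are planned: "Tau-U will be used to analyse the overlap between the baseline and intervention phase and the baseline and post-intervention phase". Results are then combined: "Tau-U will also be used to calculate an effect size and weighted average across all cases for the primary outcome variable". The section names no Tau-U variant, variance formula or significance level. Visual inspection of level, slope and variability, within and between phases, is planned beside the test.

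The phases differ greatly in length (Procedure). Participants are allocated to "one of four different baseline lengths (12 days, 19 days, 26 days or 33 days", with daily readings. Intervention readings come once per session, and "Where possible the first 4 sessions will take place bi-weekly, the second 4 sessions weekly and the final 4 sessions fortnightly". Twelve daily readings follow the last session. The sample is small: "We will aim to recruit 6–8 participants to the study".

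**The concern.** The quoted sentence implies a test of whether scores change by more than an existing trend would produce. The standard corrected statistic tests something else. It removes the ordering seen among baseline readings, and its null variance assumes exchangeable readings, that is, no trend at all. If loneliness falls slowly for any other reason, a short noisy baseline barely shows the fall, while the later and longer phases accumulate it.

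At stake is what a significant primary result may be said to mean. The correction is the only protection against spontaneous improvement that is built into the statistical test itself. If the sentence stands, a significant corrected Tau-U can be read as evidence that the therapy caused the change, when continuing natural improvement would give the same result.

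**Working it through.** The protocol gives no error rate for Tau-U, only a remark in Procedure that power is sufficient, so there is no figure to reproduce.

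**Inputs from the protocol.** Baseline readings nA = 12, 19, 26 or 33. Intervention readings nB = 12, one per session, the stated average. Twelve post-intervention readings. Score 0-12. Six or eight cases.

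**Assumptions.** Starting score 8, within-person SD 1.5, independent errors, two-sided 5% level with rejections counted toward improvement (nominal 2.5%), the four baseline lengths used evenly, inverse-variance pooling. Bi-weekly is read as twice a week, which puts the sessions on days 0 to 91.

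**Step 1: the statistic without noise.** Corrected Tau-U = (S_AB − S_A)/(nA·nB), with improving pairs counted as positive. If a perfect downward line continues and treatment does nothing, S_AB = nA·nB and S_A = nA(nA−1)/2. So Tau-U = 1 − (nA−1)/(2·12):
- nA = 12: 1 − 11/24 = 0.54
- nA = 19: 1 − 18/24 = 0.25
- nA = 26: 1 − 25/24 = −0.04
- nA = 33: 1 − 32/24 = −0.33

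The statistic is not centred at zero under a continuing trend. Its value depends on the allocated baseline length, and long baselines with steep, clean trends are over-corrected. This step needs no assumed slope or SD.

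**Step 2: why a slow drift hides in the baseline.** The standard error of a slope from nA daily readings is SD/√[nA(nA²−1)/12]. With SD 1.5:
- nA = 12: 1.5/√143 = 0.125 points/day
- nA = 33: 1.5/√2992 = 0.027 points/day

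A drift of 0.01-0.02 points/day is below one standard error even in the longest baseline. At 0.01/day the baseline itself moves only 11 × 0.01 = 0.11 to 32 × 0.01 = 0.32 points, so S_A stays small. Over the intervention the same drift amounts to 91 × 0.01 = 0.91 points. The post-intervention readings (days 92 to 103, midpoint 97.5) lie 97.5 + (nA+1)/2 = 104 to 114.5 days from the middle of the baseline, so they sit about 1.0 to 1.1 points lower, or roughly 0.7 to 0.8 SD.

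**Step 3: simulation with zero treatment effect.** The variance was either nA·nB(nA+nB+1)/3 or that plus nA(nA−1)(2nA+5)/18 for S_A. The ranges cover both formulas and 6 and 8 cases. Pooled rejection toward improvement:

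| Drift, points/day | Baseline vs intervention | Baseline vs post-intervention |
|---|---|---|
| 0 | 3-5% | 4-5% (first variance formula) |
| 0.005 | 8-19% | 36-66% (first formula, SD 1.5-2) |
| 0.01 | 25-45% | 94-100% over 0.01-0.02 |
| 0.02 | 70-90% | as above |

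**Step 4: sensitivity**, at 0.01/day, 6 cases, SD 1.5 and the first variance formula unless stated (baseline vs intervention / vs post-intervention):
- usual correction: 33-35% / 97%
- no correction: 42% / 99%
- correction only when the baseline trend is significant: 40% / 99%
- full Tau-U with both phase trends: 34% / 94%
- all sessions weekly: 42% / 91%
- SD 2: 23-24% / 84-85%
- slopes varying between cases around 0.01 with SD 0.01: 32% / 82%
- mean slope 0 with between-case SD 0.01: 7% / 16%
- one participant alone: about 12% / 38-40%

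The correction improves little on no correction.

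**Step 5: candidate remedies.**
- A per-case regression on day with a phase step, pooled, rejects toward improvement in 2-4% of runs under linear drift. It has 92-99% power for an immediate 1.5-point drop but only 9-10% for a 2.5-point effect building over 45 days. If that effect builds over the full 91 days, detection is about 1% or less and the mean coefficient has the wrong sign (about +0.2, toward worsening).
- With natural improvement that levels off (2 points, time constant 20-40 days), the same regression falsely signals improvement in 12-24% of runs.
- Projecting the baseline trend forward by Theil-Sen is worse: 15-25% false signals with no trend and 23-80% with one.

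**The case against.** The strongest reply has four parts.

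- **The drift is assumed.** This stands. The protocol gives neither slope nor SD, and the Introduction reports that many young people follow stable-high (22%) or rising (18%) courses. A reader might infer that 30-90% of pooled analyses would be false positives. The documents do not support that as a flat statement: it needs a drift of about 0.01-0.02 points/day in the same direction in most cases. Shared drift is possible, since participants start concurrently, entry requires a high UCLA-LS-3 score, and the protocol itself asks about COVID-19 and other events. It is not established.
- **The design has other safeguards.** This partly stands. Randomised staggered starts and between-phase visual analysis are sound grounds for causal inference, and Limitations urges caution and a later RCT. It would therefore be wrong to infer that the trial must misattribute change or cannot support a causal statement. But neither safeguard enters Tau-U, so neither makes the sentence about Tau-U true. The stagger spans only 33 − 12 = 21 days.
- **The sentence speaks only of trends in baseline scores, and the variant may be fixed in an analysis plan not shown.** The first half of the sentence does say that; the second half goes on to attribute change to the intervention. The variants tried all fail to deliver it.
- **A regression gate would do harm.** This stands. A reader might conclude that attribution should depend on a significant phase step. The first two sessions are assessment and formulation, so an abrupt drop at session 1 is not the expected pattern, and Step 5 shows that such a rule would nearly always miss a gradual effect.

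**Conclusion.** The protocol credits baseline-corrected Tau-U with a property it lacks. That conclusion rests on the form of the statistic and holds without any assumed slope. A significant value shows non-overlap between phases; it does not separate an intervention effect from a trend that continues.

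How often this would mislead depends on unknowns. Under the stated assumptions the baseline-versus-intervention rate runs from close to nominal with no drift to 70-90% at 0.02 points/day. The post-intervention contrast is the more exposed, near certainty at 0.01-0.02. With drifts that differ in direction between cases, the excess is modest. The point concerns what may be claimed from the primary test; it does not show that any particular drift exists.

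**What to change.** In Primary outcome measure:

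1. Delete the statement that Tau-U identifies whether change results from the intervention. Say instead that, for both contrasts, it describes non-overlap between phases and does not remove a trend continuing beyond the baseline. Keep it as the overlap effect size, with the weighted average.
2. Rest any causal statement on whether change coincides with the randomised, staggered start of intervention in the between-phase visual analysis. For baseline versus post-intervention, report improvement over time that is not separable from a continuing trend.
3. Add a sensitivity analysis, reported but not used as a gate: per case, regress score on day and phase, allow the slope to change at the start of intervention, and pool across cases. State its limits. It assumes a linear untreated trend. A step-only version has almost no power for a gradually building effect and can give it the wrong sign. It can signal falsely when natural improvement levels off. The slope-change version was not simulated here, and Step 2 shows that baseline slopes will be imprecise, most of all in the 12-day group.

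The cost is one extra analysis on data already planned and a weaker causal claim. No new data are needed.
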